### Internal validity assessment

The internal consistency reliability of the final version of the KATITA questionnaire will be evaluated with Cronbach’s alpha for the full scale and for each dimension if a multidimensional scale is obtained, with 95% confidence intervals estimated by bootstrapping. It is generally accepted that for a scale to have clinical application its Cronbach’s alpha must be above 0.80. This statistic will also be used to refine the questionnaire: leaving-one-out Cronbach’s alpha, a Cronbach’s alpha computed excluding one item in turn, should be somewhat smaller than the scale’s Cronbach alpha, otherwise it means that the left-out item is not contributing to the internal consistency reliability. Should factor analysis point to a multidimensional scale, Cronbach’s alphas will be computed for each subscale as well. The same final version of KATITA will be assessed for test-retest reliability using the two-way mixed-effects model, absolute agreement, intraclass correlation coefficient. The generally accepted cutoffs for the coefficient will be adopted: less than 0.50 (poor reliability), 0.50–0.75 (moderate reliability), 0.75–0.90 (good reliability) and greater than 0.90 (excellent reliability). For the evaluation of convergent validity with differentiation by known groups, the Wilcoxon-Mann-Whitney ranksum test will be used to compare KATITA scores between levels of risk factors for non-adherence to immunotherapy medication.

#### External validity assessment

For the analysis of the scale sensitivity to change, the time interval between baseline and transplantation will be presented by the median and interquartile range, and the change will be tested with the Wilcoxon signed rank test comparing baseline to 3-month scores. The magnitude of the change will be interpreted using the standardized response mean (SRM), which is the mean difference between baseline and 3-month post-transplant scores divided by its standard deviation [48], as moderate if SRM>0.5, or large if SRM>0.8. For the evaluation of concurrent validity, Spearman’s rho will be used to estimate the correlation between KATITA scores and the scores of the BAASIS and the CEAP-VIH scales, and the Wilcoxon-Mann-Whitney ranksum test will be used to test the difference in KATITA scores between adherent and non-adherent according to BAASIS. For the evaluation of the predictive validity of the KATITA questionnaire, the AUROC, sensitivity, specificity, positive predictive value and negative predictive value, and corresponding 95% confidence intervals, will be computed for pre-transplant KATITA scores. Structural equation modeling will be used for confirmatory factor analysis, with goodness of fit evaluated with the chi-square test/degrees of freedom statistic, Root Mean Square Error of Approximation (RMSEA), Comparative Fit Index (CFI), Tucker-Lewis index, standardized root mean squared residual and coefficient of determination.

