**Fig 3 pone.0305953.g003:**
[figure not shown]
Diagram of the study design of the external validation study.

At the pre-transplantation, baseline evaluation, demographic and clinical data will be collected, and the KATITA questionnaire will be administered. The questionnaire data will be used for the assessment of predictive validity and of structural validity, which will evaluate whether the factor structure of the KATITA questionnaire is reproduced in this different population. The timing of kidney transplantation after the baseline visit will be variable but expected to be within a short time lag. The next study visit will be at 3 months post-transplant and its purpose will be to assess the concurrent validity of the questionnaire. Concurrent validity is demonstrated by shown a high correlation of the scores of the test scale with those of a validated scale measuring the same or a closely related construct. However, there is no available scale measuring predisposition to medication non-adherence in kidney transplant patients in the pre-transplant setting. To overcome this difficulty and to still obtain a measure of concurrent validity, in addition to the re-administration of the KATITA questionnaire the following two scales were selected to be compared with KATITA at three months post-transplant. The Basel Assessment of Adherence to Immunosuppressive Medication Scale (BAASIS), a widely used questionnaire for assessing adherence to immunosuppressive drugs in adult and adolescent post-transplant recipients, consists of four questions inquiring the patient about the past occurrence of medication non-adherence episodes, two being about the frequency of missed medications doses, one on non-compliance with medication timing, and one asking about having reduced medication doses. Each question has six possible responses, from never (0 points) to everyday (5 points), and thus the questionnaire scores range from 0 to 20, with a score greater than zero classifying the patient as medication non-adherent. The CEAT-VIH scale [29] will also be applied and used as another reference against which the KATITA scores will be compared. This scale was developed to assess medication adherence of persons living with HIV infection and, in addition to questions about non-adherence episodes, includes questions assessing patients’ behavior and beliefs towards their medication. It is a 20-item scale forming a score between 18 and 92, lower scores indicating lower adherence to medication. This scale was selected because it produces an ordinal score measuring the degree of medication non-adherence, which is a distinctive feature from virtually all other medication adherence instruments that only discriminate between adherents and non-adherents, but also because HIV therapy has the same requirements as immunosuppressive therapy in transplant patients regarding strict adherence to the prescribed frequency, dosage, and timing of medication administration. The month 3 study visit will also offer the opportunity of testing KATITA’s sensitivity to change, the ability to respond to a change in state regardless of its clinical relevance to the patient or the clinician, by evaluating whether there was variation in the scale scores after patient exposure to immunosuppressant medication since the pre-transplant evaluation.

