### Sample sizes

For the focus group, eight patients will be selected, which is within the recommended size for focus groups [37]. For the cognitive interviews, sample size will be determined by saturation, that is, when no new information is obtained from participants, but it expected to require no more than 10 patients. For the development of questionnaires measuring a latent construct using factor analysis, and for reliability assessment, there are neither theoretical foundations, nor formal methods of estimation of the required sample size, and the required numbers are based on rules of thumb suggested by several authors, with some recommending a sample size defined by a ratio of participants for each scale item, often 10:1 [38], while others propose a fixed number of participants, independent of the number of items, most commonly in the range of 200 to 300 subjects [39–42]. Accordingly, the sample size for this part of the study will be no less than 300 patients. For the test-retest reliability analysis, a sample size of 20 subjects would be sufficient to ensure 80% power with an alpha error of 0.05 to identify a correlation greater than 0.60, however such small sample will not provide adequate robustness to the results, so a minimum sample size of 60 patients was defined.

The sample size for the external validity study is determined by the requirements for the evaluation of the predictive validity of the KATITA questionnaire. Assuming that the area under the ROC curve (AUROC) of the questionnaire in the prediction of immunosuppressive medication non-adherence would be at least 0.75, and that the proportion of non-adherent patients in the first 12 months after transplant will be about 50%, a sample of 364 patients would estimate the AUROC with an error of ±0.10 with 95% confidence [43]. The same sample size will be used in confirmatory factor analysis for assessment of structural validity of the factorial model, scale sensitivity to change, and concurrent validity assessment.

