### Statistical analysis

STATA 18 statistical program (Stata Corp., College Station, TX, USA) will be used for statistical analysis. All tests will be two-tailed and results will be considered statistically significant when p<0.05.

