### Questionnaire development

Exploratory factor analysis will be used for questionnaire development. Only those factors with an eigenvalue greater than 1, that is, factors that explain the variability in the scale more than a single item (Kaiser criterion), will be retained. If factor rotation is considered necessary to improve item selection, a varimax rotation, which is an orthogonal rotation, will be applied. Factor loadings less than 0.40 will be ignored. Items presenting a commonality significantly lower than the value observed for the remaining items will also be discarded. Pearson’s correlation will be used for item analysis and the following rules will be adopted for item reduction: inter-item correlations should not be greater than 0.70, which may indicate redundancy, neither less than 0.30, which suggests the item is measuring something different; item-test correlation, the correlation of each item with the scale score, should be high (>0.30), otherwise the item is probably measuring something different; item-rest correlation, the correlation of each item with the score formed with the remaining items, should be moderately low (between 0.30 and 0.70), otherwise the item may be redundant [28]. If a multidimensional scale is obtained, the item-to-own dimension correlation, the correlation of each item with the total score of its own subscale, should be high (>0.30). The assumption of independence of the factors will be tested with an inter-dimension correlation matrix and will be discarded if correlations are moderately high (>0.60).

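### Against BAASIS, the only planned effect size for concurrent validity is a Spearman rho limited by the share of patients scoring 0; the AUROC with its 95% CI should be reported beside the rank-sum test

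*Protocol article*

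**What the plan says.** The External validity section of the protocol article gives the criterion: "Concurrent validity is demonstrated by shown a high correlation of the scores of the test scale with those of a validated scale". The article concedes that no scale of predisposition to non-adherence exists for use before transplant. It therefore re-administers KATITA at month 3 alongside two comparators, BAASIS and CEAT-VIH.

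BAASIS totals run from 0 to 20, and patients are classified on them "with a score greater than zero classifying the patient as medication non-adherent".

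The External validity assessment section gives two analyses:
- for the correlation, "Spearman’s rho will be used to estimate the correlation between KATITA scores and the scores of the BAASIS and the CEAP-VIH scales" (the last name is evidently CEAT-VIH);
- for the comparison of groups, "the Wilcoxon-Mann-Whitney ranksum test will be used to test the difference in KATITA scores between adherent and non-adherent according to BAASIS".

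The general rule in the Statistical analysis section is "All tests will be two-tailed and results will be considered statistically significant when p<0.05". The Sample sizes section applies the same 364 patients to concurrent validity. AUROC with a 95% CI is planned only for predictive validity, on pre-transplant scores.

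**The concern.** Two quantities will describe how KATITA relates to BAASIS, and neither shows clearly how well it separates the two BAASIS groups.

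Rho is an effect size, but all adherent patients share the score 0. The larger that tied block, the smaller the rho that even a well-discriminating KATITA can reach. Read against the criterion of a high correlation, a modest rho could reflect a weak scale or simply few non-adherent patients at month 3.

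The rank-sum test does address group separation, but its p-value carries no magnitude. At this sample size it can be significant when separation is slight.

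What is at stake is how one named validation objective is interpreted. A well-discriminating scale could be under-rated because of the composition of the sample, and a reader shown only a significant test would not know how large the difference is.

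**Working it through.** **Inputs from the protocol article**
- N = 364, also for concurrent validity (Sample sizes).
- Two-sided 5% level (Statistical analysis).
- BAASIS from 0 to 20, non-adherent if above 0 (External validity).
- Planning AUROC 0.75 and about 50% non-adherent over 12 months (Sample sizes). Both belong to the predictive analysis.

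**Assumptions**
- Share p of BAASIS non-adherent patients at month 3: not stated. I use 20% to 50%, with 10% as a sensitivity value. The Introduction cites 20% to 54% for non-adherence in general.
- KATITA is treated as continuous and oriented so that higher means more predisposed.
- AUROC 0.75 serves only as an illustration.

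**The plan's own figure.** With 182 per group and AUROC 0.75, the Hanley-McNeil terms are 0.75/1.25 = 0.600 and 2 × 0.5625/1.75 = 0.643. The variance is [0.1875 + 181(0.600 − 0.5625) + 181(0.643 − 0.5625)]/182² = 0.00065, so SE = 0.0255 and the 95% half-width is 0.050. The 364 thus reproduces if the 0.10 in the text is the full interval width, not a half-width. That is a separate matter and does not affect this point.

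**Step 1: rho implied by a given AUROC, two-level BAASIS.** rho = (2 × AUROC − 1) × √(3p(1 − p)). At AUROC 0.75 the first factor is 0.5. At AUROC 1 it is 1, which gives the ceiling.

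| p | √(3p(1 − p)) = ceiling | rho at AUROC 0.75 |
|---|---|---|
| 10% | √0.27 = 0.52 | 0.26 |
| 20% | √0.48 = 0.69 | 0.35 |
| 35.6% | √0.688 = 0.83 | 0.41 |
| 50% | √0.75 = 0.87 | 0.43 |

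**Step 2: does grading above 0 rescue rho?** In a bivariate-normal simulation (400,000 draws, calibrated to AUROC 0.75, adherent patients tied at 0), rho was 0.26 at 10%, 0.35 at 20%, 0.44 at 35.6% and 0.48 at 50%. If severity above 0 is unrelated to KATITA, it is about 0.40 at 50%. The ceiling with no ties among non-adherent patients is √(1 − (1 − p)³): √(1 − 0.512) = 0.70 at 20% and √(1 − 0.729) = 0.52 at 10%. At low shares, grading adds almost nothing.

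**Step 3: smallest AUROC with rank-sum p<0.05.** AUROC = 0.5 + 1.96 × √((N + 1)/(12·n1·n2)).
- 50% (182/182): 0.5 + 1.96 × √(365/397,488) = 0.559.
- 35.6% (130/234): 0.5 + 1.96 × √(365/365,040) = 0.562.
- 20% (73/291): 0.5 + 1.96 × √(365/254,916) = 0.574.

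By the Step 1 formula, rho at each of these limits is about 0.10. For a true AUROC of 0.60, power is about 92% at 50% and 75% at 20%. If only 291 patients were analysed (an assumed 20% loss), the limits move to 0.566 at 50% and 0.583 at 20%.

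**The case against.** Four objections stand and limit the point.

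- **No p-value rule.** A reader might infer that p<0.05 alone would establish concurrent validity. The article does not say so. It defines statistical significance in general and ties concurrent validity to a correlation. Rho is reported next to the test, and at the significance limit it would be only about 0.10, so weak discrimination would show in a planned output.
- **0.75 is not the plan's target here.** The assumption "Assuming that the area under the ROC curve (AUROC) of the questionnaire in the prediction of immunosuppressive medication non-adherence would be at least 0.75" concerns pre-transplant scores against the three-method criterion at months 6 and 12, which does not include BAASIS. It cannot be said that a scale performing as planned would fail against BAASIS.
- **Cut-offs elsewhere do not define a high correlation.** A reader might set a rho of 0.35 to 0.48 against the 0.30 and 0.60 in Questionnaire development and see a contradiction. Those values govern item-level correlations and the independence of factors, not the correlation between two scales. That no numeric cut-off appears for concurrent validity may be left to a fuller document.
- **There is a second comparator.** CEAT-VIH was chosen because it yields a graded score, and rho is a natural measure for it. Rank-sum plus Spearman is also a standard pairing.

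None of this changes the behaviour of rho against BAASIS. The only planned effect size for that comparison still depends on the share scoring 0, and the test beside it still gives no magnitude.

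**Conclusion.** The point holds as an improvement that costs nothing, not as the correction of an error or contradiction. Against BAASIS, rho mixes discrimination with the month-3 share of non-adherent patients: the same AUROC of 0.75 gives about 0.26 at 10% and 0.35 to 0.48 over 20% to 50%. The criterion of a high correlation is therefore hard to read for this comparator, and a modest rho is not in itself evidence of poor discrimination. A significant rank-sum test shows only that the AUROC differs from 0.5, possibly by as little as 0.06 to 0.07.

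These figures rest on the assumed 20% to 50% range, on KATITA having few ties and, for the upper values of rho, on the latent-normal model with graded severity. The conclusion that rho depends on the share scoring 0 follows from the scoring of BAASIS alone.

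**What to change.** In External validity assessment, state that the AUROC of month-3 KATITA for BAASIS score above 0 versus 0, with its 95% CI, will be reported with the rank-sum test, and that the BAASIS part of concurrent validity will rest on that estimate. The AUROC is the planned Mann-Whitney U divided by n1·n2. Group sizes affect its precision but do not enter its value as they do rho.

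Keep Spearman's rho for BAASIS and CEAT-VIH. Report the observed share scoring 0 on BAASIS and interpret the BAASIS rho in its light. Do not adopt 0.75 as a pass mark, since it was set for another criterion and time point.

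Cost: a sentence or two in the analysis section, with no new data, visits or patients.

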#### Cross-cultural validation

A confirmatory factor analysis using structural equation modeling will be conducted to test the factor structure. Internal consistency reliability will be assessed with Cronbach’s alpha. Test-retest reliability will be evaluated with the two-way mixed-effects model, absolute agreement, intraclass correlation coefficient.

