## Abstract

Non-adherence to immunosuppressive medication after kidney transplant is an important cause of graft rejection and loss. Approaches to minimization of non-adherence have focused on the identification of episodes of medication non-adherence, but by then irreparable harm to the graft may already have occurred, and a more effective approach would be to adopt preventive measures in patients who may have difficulty in adhering to medication. The aim of this study protocol is to develop and validate a clinical questionnaire for assessing, in kidney transplant candidate patients in the pre-transplant setting, the predisposition to non-adherence to immunosuppressive medication. In this multicenter, prospective study, a pilot questionnaire in Brazilian Portuguese language, composed of Likert-scaled statements expressing patients’ beliefs, behaviors and barriers regarding medication taking will be assembled from a literature review, from focus groups, and an expert panel. The pilot questionnaire will be administered to a minimum of 300 patients in kidney transplant waiting lists and exploratory factor analysis will be used for development of the definitive questionnaire. A random subsample of a minimum of 60 patients will have the scale re-administered after one month for evaluation of test-retest reliability. A multicenter, external validation study will include 364 kidney transplant candidates who will be evaluated immediately before surgery and at months 3, 6 and 12 post-transplant for assessment of concurrent validity, by comparison with two scales that assess medication non-adherence, and for determination of predictive validity using a triangulation method for assessment of medication non-adherence. Structural validity will be assessed with confirmatory factor analysis using structural equation modeling. Cross-cultural generalizability and validity will be assessed by a multicenter study, in which a translation of the scale to another language will be administered to kidney transplant candidate patients from a different culture, with a subsample being selected for test-retest. This study will be conducted in Spain with a Spanish translation of the scale.

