## Materials and methods

### Objectives

The objectives of each project phase are as follows: First phase, development of a psychometric scale: 1) to develop a comprehensive item pool for KATITA; 2) to identify the psychometric dimensions of medication non-adherence in the pre-transplant setting; 3) to select the relevant items composing the final KATITA questionnaire. Second phase, internal validation study: 1) to evaluate internal consistency reliability of KATITA; 2) to evaluate test-retest reliability of KATITA; 3) to evaluate construct validity by assessing convergent validity. Third phase, external validation study: 1) to evaluate criterion validity by assessing concurrent validity and predictive validity; 2) to evaluate the scale structural validity. Fourth phase, transcultural adaptation to a different language: 1) to translate KATITA to a different language using the translation-back translation method; 2) to evaluate reliability of the KATITA translation using internal consistency and test-retest reliability methods.

The study protocol was approved by the Research Ethics Committee of the coordinating center at Hospital Universitario Onofre Lopes in Natal-RN, Brazil (authorization number 3.179.920 of March 1, 2019). All four study phases are considered minimal risk research, no experimental interventions will be performed on patients, and no additional data will be collected beyond the necessary for usual routine care. Approval will be obtained from the Institutional Review Boards of every collaborating center and signed informed consent will be obtained from all participating patients.

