
### Cross-cultural validity

In the fourth study phase, the KATITA questionnaire will be evaluated for cross-cultural generalizability and validity, that is, whether the questionnaire’s properties remain consistent and applicable when used in diverse cultural settings, and that the measurements remain valid and accurate across various cultural groups. The country selected for this study was Spain because it has had the world’s greater number of kidney donors per million population for over 30 years [35].

The cross-cultural adaptation will be performed according to the Guillemin protocol [36], starting with the Spanish translation of the KATITA questionnaire made by a native speaker of the language, which will be evaluated semantically by kidney transplant experts and patients to ensure conceptual equivalence. The Spanish text will be back translated into the original Portuguese language by a linguistic specialist without connection to the clinic and without knowledge of the original text. This process will continue iteratively until the final version of the instrument is agreed among the participants of the process. A multicenter prospective study will enroll Spanish patients consecutively observed in two kidney transplant centers and two hemodialysis clinics in Barcelona, Spain, with the same eligibility criteria of the external validity study: patients in the kidney transplant waiting list, of both sexes, over 18 years-old, excluding hospitalized patients, those planned for retransplant or recipients of additional non-kidney transplant, and illiterate patients or with impaired cognition. Demographic and clinical data will be recorded and patients will be asked to self-rate the translated questionnaire. A subsample of patients will be consecutively selected and invited to have the questionnaire re-administered one month later. This will conclude the KATITA’s study plan.

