For the cross-cultural generalizability and validation study, the sample size is defined as 5 patients per questionnaire item. This number was based on a systematic review of 114 articles reporting on the validation of psychometric scales, where the authors [44] concluded that there is no formal method to calculate the sample size to validate clinical questionnaires. In that review they reported that in 50% of the articles, the sample size was 10 subjects or less per questionnaire item. Other authors have proposed that the calculation of the sample size in a validation study of clinical questionnaires be determined based on the number of items in the questionnaire. Kline [45] proposed 2 subjects per variable, Hatcher [46] suggested 5 per item and a minimum of 100 subjects. Nunnally [38] suggested 10 per item and Pett et al. [47] 10–15 participants per item. Thus, the proposed proportion of 5 subjects per questionnaire item seems adequate for the purposes of this study. For the test-retest reliability assessment, again a subsample of 60 patients will be selected.

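### Phase four claims cross-cultural validity, but no planned statistic tests whether Spanish and Brazilian item loadings or intercepts are equal

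*Protocol article*

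**What the plan says.** The article states the purpose of phase four in two ways.

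- **Broad aim.** The Abstract says "Cross-cultural generalizability and validity will be assessed by a multicenter study, in which a translation of the scale to another language will be administered". The Cross-cultural validity section sets the target more fully, asking in effect for scores with this feature: "properties remain consistent and applicable when used in diverse cultural settings, and that the measurements remain valid and accurate across various cultural groups".
- **Narrow aim.** The Objectives section lists two items for the phase: to translate the scale, and "to evaluate reliability of the KATITA translation using internal consistency and test-retest reliability methods".

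The Cross-cultural validation section of the statistical analysis names three analyses:

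- For structure: "A confirmatory factor analysis using structural equation modeling will be conducted to test the factor structure".
- For coherence of the items, Cronbach's alpha.
- For stability over time: "Test-retest reliability will be evaluated with the two-way mixed-effects model, absolute agreement, intraclass correlation coefficient".

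The phase enrols Spanish patients at two transplant centres and two hemodialysis clinics in Barcelona. They supply demographic and clinical data and complete the translated questionnaire, and a subsample repeats it. No adherence outcome or comparator scale is listed. On size, Sample sizes says "the sample size is defined as 5 patients per questionnaire item", with 60 patients for the retest. The Cross-cultural validity section also plans translation, back-translation and a semantic evaluation by experts and patients.

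**The concern.** The broad aim concerns one group relative to another. It needs evidence that a Spanish and a Brazilian patient with the same predisposition tend to give the same item answers. The three named statistics describe the Spanish sample by itself. If a translated item is easier or harder to endorse in Spain, or relates differently to the construct, all three can still look good.

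What is at stake is the conclusion of the phase. A good alpha, ICC and model fit could be reported as cross-cultural validity when comparability of scores was never tested.

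**Working it through.** The plan gives no figure on this point to reproduce, so the check is of what each planned statistic can respond to.

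**1. Algebra.** Let every Spanish patient's answer to item j rise by a constant c_j.

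- Covariances: Cov(x_j + c_j, x_k + c_k) = Cov(x_j, x_k), so the covariance matrix S is unchanged.
- Alpha = k/(k − 1) × (1 − Σ s_jj / s²_total). It depends on S only, so it is unchanged.
- Single-group CFA by maximum likelihood: F = ln|Σ| + tr(SΣ⁻¹) − ln|S| − p. It depends on S only, so chi-square/df, RMSEA and CFI are unchanged.
- Absolute-agreement ICC: both administrations rise by the same total, so the between-patient, between-occasion and residual mean squares are unchanged.

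**2. Size of the hidden shift.** Assumptions not in the documents: one factor, p items with unit variance and loading 0.6, and Spanish intercepts raised by 0.5 SD on one third of the items. The total then moves by m × 0.5 / √(p + p(p − 1) × 0.36), where m is the number of shifted items.

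| Items p | Spanish n (5 per item) | m | Shift in total | SD of total | Shift in SD | Simulated |
|---|---|---|---|---|---|---|
| 15 | 75 | 5 | 2.5 | √90.6 = 9.52 | 0.26 | 0.25 |
| 20 | 100 | 6 | 3.0 | √156.8 = 12.52 | 0.24 | 0.24 |
| 30 | 150 | 10 | 5.0 | √343.2 = 18.53 | 0.27 | 0.28 |

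**3. What the planned statistics show.** Simulation with the same assumptions, continuous responses, 60 replicates, 364 Brazilian patients, equal latent means, 20 items and 100 Spanish patients (ICC on 60):

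| Spanish sample | Alpha | ICC | RMSEA | CFI | Total vs Brazil |
|---|---|---|---|---|---|
| Equivalent to Brazil | 0.916 | 0.872 | 0.027 | 0.972 | 0.00 SD |
| Six intercepts raised 0.5 SD | 0.916 | 0.872 | 0.027 | 0.972 | 0.24 SD |
| Loadings 0.8/0.4 against 0.6 | 0.919 | 0.885 | 0.025 | 0.983 | 0.00 SD |

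The first two rows agree in every planned statistic. The third shows that clearly unequal loadings also pass. A Spanish CFA does estimate the Spanish loadings, but nothing in the plan compares them with the Brazilian ones.

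**4. Bounded items.** The pilot items are scored as integers from 0 to 4, so a shift identical for every patient is not literally possible. Floor or ceiling effects alter the covariances somewhat. The invisibility is then approximate, but the statistics still do not test equivalence.

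**The case against.** Six points can be made in the plan's favour.

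- **The formal objective is reliability.** Alpha and the ICC answer the Objectives section, and the CFA goes beyond it. This stands. The fault is an inconsistency between sections, and a narrower claim would cure it too.
- **Equivalence is addressed qualitatively.** A reader might infer that phase four has no evidence of equivalence at all. That goes too far. The semantic review addresses conceptual equivalence, and a well-fitting Spanish CFA supports the same factor pattern. Neither tests loadings or intercepts.
- **The article is condensed.** It does not say in so many words that the CFA is single-group. But the section names its methods, the sample it describes is Spanish, and no comparison appears anywhere. The point is a mismatch between stated aim and named methods, not missing detail.
- **No cut-off is carried to Spain.** A reader might infer that a Brazilian threshold will misclassify Spanish patients. No section plans to pool or compare scores across countries or to apply a Brazilian cut-off in Spain, so this would be an assumed later use.
- **The Brazilian records are not wasted.** The 364 external-validation patients have their own CFA. They are only not stated to be used in phase four.
- **The comparison is imperfect.** The Brazilian patients had just been scheduled for transplantation, while the Spanish patients are on the waiting list. Non-invariance could therefore reflect stage of care as well as culture. Power is also limited. In a simulation of 100 replicates (continuous items, loadings 0.6, 364 against 75 to 100 patients), a CFI-drop rule caught 0.5-SD shifts on four items in 98-100% of runs, 0.3-SD shifts on four items in 54-58%, and a 0.5-SD shift on a single item in 35-40%. Both limits stand and belong in the plan.

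**Conclusion.** The concern holds in this form: the Abstract and the Cross-cultural validity section claim more than the named analyses can test, and the Objectives section claims less than either. None of the planned statistics tests equal loadings or intercepts between Spain and Brazil.

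Under the stated assumptions, a half-SD intercept shift on a third of the items would move totals by about a quarter of an SD with no visible sign. The item count, loadings and shifts are assumptions. The exact result applies to additive shifts and holds approximately on 0-4 items. Nothing here shows that such a shift will occur, or that the translation is poor. The planned reliability analyses are sound for the reliability objective and should stay.

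**What to change.** In the Cross-cultural validation section:

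1. Add a two-group CFA of the Spanish sample against the Brazilian external-validation baseline sample. Test configural, then metric, then scalar invariance. Leave latent means free to differ.
2. Fix the criterion in advance, for example a CFI drop of no more than 0.01 at each step, and report the non-invariant items by name.
3. State that the Brazilian patients were just scheduled for transplant and the Spanish patients are wait-listed, so non-invariance may reflect stage of care as well as culture.
4. State that, with 5 Spanish patients per item, a pass does not exclude modest item shifts.
5. If the comparison is not made, or invariance fails, limit the phase-four conclusion to translation, reliability and factor structure in Spain.

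Then align the Abstract, the Objectives and the Cross-cultural validity section with whichever claim is kept.

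The cost is wording and a little analyst time. No new patients or data are needed, and Stata's sem command supports multi-group models. The downside is that the validity claim can now fail.
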